#### Laboratory safety variables

Hematology and clinical chemistry data will be summarized at each scheduled assessment and presented by NCI CTCAE toxicity grade (version 4) (see Appendix 7: section 10.7).

In case of relevant abnormalities on the laboratory variables detected from statistics tabulations, the data will be presented graphically using a plot of mean level versus time by treatment group and/or a Pre/post treatment scattergram for each relevant laboratory variable (Figure 9 and 10 respectively).

**Tables on Laboratory safety variables:**

Quantitative descriptive statistics will be tabulated for each laboratory variable at each time over the course of the study (e.g., at each visit) on raw values and change from baseline (Statistical Table 41 and 44).

**Qualitative descriptive statistics:**

- Qualitative descriptions statistics will be tabulated for each laboratory variable at each time over the course of the study overall and by treatment group (Statistical Table 42 and 45):
  - By clinical significance (normal, abnormal NCS, abnormal CS)
  - By CTCAE grade
- Shift Tables between CTCAE grade or clinical significance for each laboratory results comparing baseline to each visit (Statistical Table 43 and 46).

A listing of all safety-related laboratory tests (Listing 16.2.8.1 and 16.2.8.3) will be prepared, presenting patient id, identification of time point, Age, Sex, weight and IMP dose, identification of laboratory test, result, flagged as abnormal when abnormal and normal range when available and relevant, toxicity grading when available. This listing will be presented by study site and by study treatment.

A patient listing of abnormal laboratory values will also presented (Listing 16.2.8.2 and 16.2.8.4)

#### Vital signs

For all vital signs recorded, quantitative descriptive statistics will be computed by visit (and treatment group on both raw values and change from baseline to each visit (Statistical table 47). All individual measurements will be provided in Listing 16.2.9.1.

#### **Physical examinations**

For all the variables collected during physical examinations, the frequencies of normal, abnormal NCS and abnormal CS values will be reported by visit and treatment group (Statistical table 48). All individual measurements will be provided in Listing 16.2.9.2.

#### **Injection site inspection**

Descriptive statistics for the global assessment of injection site completed by the investigator will be computed for each visit (at each treatment administration) by treatment group (Statistical table 49).

#### **ECG**

For 12-lead ECG assessments variables collected, the frequencies of normal, abnormal NCS and abnormal CS values will be reported by visit and treatment group (Statistical table 50). All individual measurements will be provided in Listing 16.2.9.3.

#### **ECOG performance status**

For ECOG performance status, the frequencies of each grade will be reported by visit and treatment group (Statistical table 51). All individual assessments will be provided in Listing 16.2.9.4.

#### **Prior and Concomitant medication**

Concomitant medication will be coded using the WHO DD thesaurus. Coding will be agreed upon with the sponsor before data base lock.

"Concomitant" is defined as a medication which was taken during treatment, e.g. stop date later than randomization date or start date before 4 weeks after end-of-treatment visit.

The medications reported prior to the baseline visit are:

- medications taken prior to randomization and related to NSCLC treatment (including response to treatment)
- medications taken in the 2 weeks prior to randomization and not related to NSCLC treatment,

Note: vitamins and/or dietary supplements are not considered concomitant medications.

Prior and concomitant medication will be tabulated by treatment group with the number and percentage of patients with prior medication classified by therapeutic class (level 2) and preferred name (Statistical table 17, Statistical table 52 respectively).

A by patient listing of concomitant medication will also be provided in Listing 16.2.10.4.

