### **Major protocol deviations**

Major protocol deviations are defined as deviations liable to prevent or change the interpretation of the results of the primary efficacy analysis of the study. The following deviations may be considered as major (this list is not exhaustive and will be reviewed at the time of the blind review meeting):

- non compliance with the inclusion or non inclusion criteria
- non compliance with the randomisation procedure
- non compliance with study treatment
- no post-baseline data for the primary efficacy endpoint
- intake of forbidden medication

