## Data handling conventions

### Baseline definitions

The measurements taken on baseline visit are assumed to be baseline values for the respective parameters.

Baseline visit, which takes place on day 1 of week 0, should be performed within 4 weeks after administration of the last cycle of first-line platinum-based chemotherapy.

The following characteristics will be measured at baseline visit:

- Physical examination and vital signs (blood pressure and pulse rate after 5 minutes sitting, body temperature and body weight, height)
- ECOG Performance Status.
- Electrocardiogram (12-lead ECG).
- Hematology.
- Clinical chemistry.
- Collection of blood sample for immunomonitoring. Samples will be collected before drug administration.

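### The only date rule for concomitant medication is true of every record with valid dates, so it cannot separate concomitant from prior medication

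*SAP*

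**What the plan says.** The SAP section Prior and Concomitant medication (under Safety analyses) starts from a verbal definition: "Concomitant' is defined as a medication which was taken during treatment, e.g". The example that follows is the only date criterion the SAP gives: "stop date later than randomization date or start date before 4 weeks after end-of-treatment visit".

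The same section then lists what is reported as taken before the baseline visit:

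- "medications taken prior to randomization and related to NSCLC treatment (including response to treatment"), and
- "medications taken in the 2 weeks prior to randomization and not related to NSCLC treatment".

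It makes one explicit exclusion: "vitamins and/or dietary supplements are not considered concomitant medications". Prior and concomitant medication go to separate outputs ("Statistical table 17, Statistical table 52 respectively"), and concomitant medication is also listed by patient in Listing 16.2.10.4.

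Concomitant medication is named under Safety endpoints as one of the items by which safety is evaluated. Section 8 (Derived data) contains no derivation for it, so the date criterion above is all a programmer has.

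**The concern.** The verbal definition and the two separate tables show that the SAP means to distinguish medication taken before treatment from medication taken during it. The date criterion does not make that distinction. Its second condition alone admits any drug that started before the cut-off of 4 weeks after the end-of-treatment visit, and so every drug that both started and stopped before randomisation. Its first condition alone admits any drug that stopped after randomisation, however late it began.

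At stake is whether Table 52 and Listing 16.2.10.4 can describe co-treatment during the vaccination period. If the criterion is programmed as it stands, they take in all the prior medications as well, and a reader cannot tell which drugs overlapped with study treatment.

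**Working it through.** The SAP gives no figure to reproduce here; the check is one of logic.

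**Inputs.** From Prior and Concomitant medication:

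- Condition A: stop date > randomisation date.
- Condition B: start date < end-of-treatment visit + 4 weeks (28 days).
- Connective: *or*.

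Assumptions: both dates are complete, a drug does not stop before it starts, and the end-of-treatment visit is not before randomisation.

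**Proof.** A record fails A *or* B only if it fails both:

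- not A: stop ≤ randomisation;
- not B: start ≥ end of treatment + 28 days > randomisation.

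Together these give start > randomisation ≥ stop, so the drug would start after it stopped. No valid record can do so, and the rule is always true.

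**Enumeration.** Put randomisation at day 0 and the cut-off at L = end-of-treatment day + 28. Take every pair of whole days with stop ≥ start from day −200 to day L + 200. That is N = L + 401 days and N(N + 1)/2 pairs. Under *and*, two groups drop out:

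- stop ≤ 0: days −200 to 0, giving 201 × 202/2 = 20,301 pairs;
- start ≥ L: days L to L + 200, giving another 20,301 pairs.

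The end-of-treatment days below are illustrative assumptions.

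| End of treatment (day) | All pairs | Accepted with *or* | Accepted with *and* |
| --- | --- | --- | --- |
| 0 | 92,235 | 92,235 | 51,633 |
| 21 | 101,475 | 101,475 | 60,873 |
| 126 | 154,290 | 154,290 | 113,688 |
| 364 | 314,821 | 314,821 | 274,219 |

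For day 126: L = 154, N = 555, 555 × 556/2 = 154,290, and 154,290 − 2 × 20,301 = 113,688. The counts show that nothing is excluded under *or*. They do not estimate a share of real records, because that depends on the range of days chosen.

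**Examples, end of treatment at day 126 (cut-off day 154).**

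| Course (days) | *or* | *and* |
| --- | --- | --- |
| −91 to −28 | concomitant | not |
| −10 to −3 | concomitant | not |
| −30 to 60 | concomitant | concomitant |
| 20 to 25 | concomitant | concomitant |
| 200 to 260 | concomitant | not |

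**Against the rest of the SAP.** Under Missing or incomplete dates, a drug with an incomplete onset date is presumed to fall in the treatment phase unless other data point elsewhere, and a stop date before baseline is given as such data. So a pre-baseline stop counts against the treatment phase when the onset is incomplete, whereas with complete dates the same drug satisfies the concomitant criterion.

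**The case against.** The strongest reply is that the date clause is not the definition. It follows *e.g.*, so the words about being taken during treatment govern, and a course completed before randomisation fails them. The separate prior-medication list and Table 17 confirm that intent. This stands as far as it goes: misclassification arises only if the clause is programmed literally. But the clause is the only operational criterion, and it contradicts the phrase it is meant to illustrate. A programmer must either code a rule that excludes nothing or devise another.

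A second reply is that date-based assignments are confirmed or overturned at the data review meeting. That sentence sits under missing and incomplete dates, so its reach is arguable. A review may catch the problem, but it does not supply the rule.

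A reader might also infer three stronger consequences that the SAP does not support:

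- **Nearly all patients shown with concomitant platinum.** First-line chemotherapy does precede baseline, which "should be performed within 4 weeks after administration of the last cycle of first-line platinum-based chemotherapy". But the schedule has separate rows for treatment history and concomitant medications, and cancer treatment history has its own Table 9 and Listing 16.2.4.4. Whether chemotherapy also sits in the data to which the rule is applied is not stated.
- **Post-study anticancer therapy added to Table 52.** In the schedule, concomitant medications are recorded up to the end-of-treatment visit, and later treatments fall in a separate follow-up row. The two would have to be pooled, and nothing says they are.
- **Patients lost from the per-protocol set.** Section 3.1 names "intake of forbidden medication" as a deviation that may be major, but nothing ties that screen to this rule, and deviations are adjudicated at the blind review meeting.

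**Conclusion.** The point holds for the date criterion itself. For any record with complete and valid dates it is always true, so it cannot separate prior from concomitant medication, and it conflicts with both the verbal definition and the division between Tables 17 and 52. Applied literally, it makes every recorded medication except vitamins and dietary supplements concomitant.

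The certain effect is confined to Table 52 and Listing 16.2.10.4, which would repeat the prior medications of Table 17. These are descriptive outputs on a named safety endpoint. No test, estimate or analysis set is shown to change. How many patients would appear with concomitant platinum, and whether any later therapy would appear, depends on which records the medication dataset holds, and the SAP does not settle that. This is a stated rule that gives a wrong table if followed, so it is more than missing detail. Its reach is small, and it should be corrected before database lock.

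**What to change.** Replace *e.g.* with *i.e.* and *or* with *and*. A medication is then concomitant if it stopped after randomisation (or is ongoing, or has no stop date) **and** started before 4 weeks after the end-of-treatment visit. Add that medications stopped on or before the randomisation date are prior only, and that those started at or after the cut-off are post-treatment.

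This keeps the SAP's own 4-week window, so a drug started within 4 weeks after the end-of-treatment visit still counts as concomitant. The cost is one sentence in the SAP and one line of derivation code, with no new data.

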## Statistical/Analytical issues

### Adjustments for Covariates

All Cox models for all time-to-event endpoints, including for sensitivity analysis of the primary endpoint will be adjusted for the following stratification factors and prognostic factors:

- stratification factors:
  - Response to first line chemotherapy: objective response vs. stable disease,
  - Squamous vs. non-squamous,
  - Stage IV vs. recurrent stage I-III,
- prognostic factors:
  - Level of tumor TERT expression: low vs. high,
  - Vaccine specific immune response status: naturally occurring response vs. absence of naturally occurring response.

### Handling of Dropouts or Missing Data

For the primary endpoint, if no information is available on patient survival, the patient will be censored at the time of the last information available. Also, for all time-to-event analyses the same censoring approach will be used. For the 12 months survival analysis (secondary efficacy endpoint), the missing efficacy data will be imputed using the worst case approach *(i.e.* “death” for the patients randomised in the Vx-001 arm and “alive” for the patients randomised in the placebo arm).

For all other variables except missing/incomplete dates (see below), missing data will be treated as missing and no imputation will be done.

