### Determination of sample size

#### **Initial sample-size calculation:**

The initial sample-size calculation, at the time the first version of the protocol was finalized was the following:

The number of patients to enrol is estimated based on the following hypotheses:

H0: The proportion of patients with OS after 12 months of treatment in the Vx-001 group is less than or equal to that of the placebo group.

H1: The proportion of patients with OS after 12 months of treatment in the Vx-001 group is greater than that of the placebo group.

The proportion of patients in the placebo group with OS at 12 months from randomization is assumed to be **43%** (Fidias et al 2009; Ciuleanu et al 2009; Cappuzzo et al., 2010). The proportion of patients in the vaccine group with OS at 12 months from the end of first-line treatment is assumed to be **58%**.

The primary analysis will be performed after all patients have been followed up for at least 12 months. Based on the above assumptions for OS at 12 months and 200 evaluable patients (100 on the Vx-001 arm and 100 on the placebo arm), the primary efficacy analysis would have an overall power of approximately 80% to detect a difference in treatment effect at the 0.1 one-sided significance level.

Although the full analysis set (FAS, see definition in the statistical methods section) is the primary efficacy dataset, the study will be powered based on the per protocol (PP) analysis of the primary efficacy endpoint. Assuming that all randomised patients will be in the FAS, and assuming that 10% of patients in the FAS will be excluded from the PP dataset, a total of 220 patients will be randomised in the study to attain approximately 200 evaluable patients.

The study design is based on comparison of proportions in two treatment arms using an one-sided a Pearson’s chi-squared test.

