#### **Revised sample-size calculation:**

The sample size-calculation was revised as follows, following the change in the primary efficacy analysis

Assuming 50% of screened patients will experience disease control after 1st line chemotherapy, 41% of screened patients will be HLA-A*0201 positive, of whom 80% will be TERT positive in their tumour biopsy, approximately 1500 patients will be screened to enrol around 220 HLA-A*0201 positive patients with TERT expressing NSCLC with disease control after 1st line treatment (110 on the Vx-001 arm and 110 on the placebo arm), calculated using SAS® 9.2 software with a maximum of 230 patients.

The number of patients to enroll is estimated based on the following hypotheses:

H0: The proportion of patients with OS after 12 months of treatment in the Vx-001 group is less than or equal to that of the placebo group.

H1: The proportion of patients with OS after 12 months of treatment in the Vx-001 group is greater than that of the placebo group.

The proportion of patients in the placebo group with OS at 12 months from randomization is assumed to be 43% (Fidias et al 2009; Ciuleanu et al 2009; Cappuzzo et al., 2010), corresponding to an overall survival of 9.8 months, assuming exponential survival. The proportion of patients in the vaccine group with OS at 12 months from the end of first-line treatment is assumed to be 58% corresponding to an overall survival of 15.2 months, assuming exponential survival.

The primary analysis will consist in a comparison of overall survival between the two arms using the Kaplan Meier method to build survival curves and the Logrank test to compare them between treatment groups and will be performed after all patients have been followed up for 6 months. The follow-up of the patients will nevertheless continue after this primary analysis until 12 months, as planned. Based on the above assumptions for OS at 12 months and 200 evaluable patients (100 on the Vx-001 arm and 100 on the placebo arm), the primary efficacy analysis will have an overall power of approximately 82.5% to detect a difference in treatment effect at the 0.05 one sided significance level.

Although the full analysis set (FAS, see definition in Section 3) is the primary efficacy dataset, the study will be powered based on the per protocol (PP) analysis of the primary efficacy endpoint.

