### Significance testing and estimation

The analyses of the primary efficacy criterion (overall survival) including the sensitivity analysis and of twelve months survival (secondary endpoint) will use a one-sided 0.05 type-one error rate. All other inferential tests on secondary or exploratory efficacy endpoints (see Sections 5.2.4.3 and 5.2.4.5) are presented only with an illustrative purpose and will use a two-sided 0.05 type-one error rate.

For some variables identified in this SAP, confidence intervals will be calculated with a two-sided coverage of 95%.

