#### Secondary efficacy analyses

The following secondary endpoints will be analysed on the FAS and PP sets:

- Twelve months survival:

A patient overall survival (success) at 12 months is defined as a patient who is alive as confirmed by the visit at week 52. If the patient misses the visit or has been lost to follow-up, every effort will be made by the investigator to ascertain whether the patient was alive on the theoretical date of his/her week 52 visit.

A one-sided Pearson’s chi-squared test of proportions will be used to compare the survival rate of the Vx-001 treated group to the placebo treated group at 12 months (Statistical Table 22).

- Time to Treatment Failure (TTF)

Time to treatment failure is defined as the interval between the date of first study treatment and the date of early withdrawal, or the date of the initiation of other anti-tumor treatment, whichever will come first. Patients without early withdrawal or initiation of another anti-tumor treatment will be censored at their last tumor assessment of target or non-target lesions. If patient have neither any failure events nor any post-baseline tumor assessment censoring time will be set to zero.

All these secondary endpoints are "time to event" endpoints and will be analyzed via

- Kaplan-Meier curves by treatment arm and log-rank test for their comparison (Statistical Table 23, Figure 5)
- Cox regression model where the treatment effect will be included and also the stratification factors and prognostic factors specified in the section 5.2.4.2 will be also included. Via this Cox model a two-sided 95% confidence interval of the hazard ratio of the treatment effect will be provided for both population (FAS and PP sets) (Statistical Table 24, Figure 6).

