### Interim Analyses and Data Monitoring

No Data and Safety Monitoring Board has been set-up for this study.

The primary study analysis will be performed when all patients randomised will have reached 6 months follow-up. A long term follow-up analysis will be performed later when the follow-up of the study will be completed.

Two database locks will be performed. The first lock will occur for the primary study analysis. Before this first database lock, the data will be reviewed and the classification of protocol deviations will be done during the Blind data review meeting. After the first database lock, all study personnel will have access to unblinded data.

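### The only planned comparison of 12-month survival counts missing patients as dead on Vx-001 and alive on placebo, which gives a bound rather than an estimate and conflicts with the censoring rule for overall survival

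*SAP*

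**What the plan says.** SAP 5.2.4.3 (Secondary efficacy analyses) defines 12-month survival as a yes/no success, alive at week 52. It fixes the test: a one-sided Pearson "chi-squared test of proportions will be used to compare the survival rate of the Vx-001 treated group" with that of the placebo group (Table 22). Investigators are to make every effort to establish vital status on the theoretical week-52 date.

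SAP 5.3.2 (Handling of Dropouts or Missing Data) adds that for this endpoint "the missing efficacy data will be imputed using the worst case approach", meaning death on Vx-001 and alive on placebo. The same paragraph censors patients of unknown status at last information in the primary analysis and in all time-to-event analyses.

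SAP 5.1.2 says that "twelve months survival (secondary endpoint) will use a one-sided 0.05 type-one error rate". On timing, SAP 5.3.3 says: "The primary study analysis will be performed when all patients randomised will have reached 6 months follow-up". A longer-term analysis and a second database lock follow. No section says at which lock the 12-month test is run.

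Section 5.2.4.3 also describes all its secondary endpoints as time-to-event endpoints. However, the Kaplan-Meier and Cox outputs it cites (Tables 23 and 24, Figures 5 and 6) are listed in the appendices for time to treatment failure only. They supply no Kaplan-Meier comparison at 12 months.

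**The concern.** Setting missing patients to the worst outcome on one arm and the best on the other answers one question: how bad could the comparison be? That is a legitimate stress test. Here it is the sole analysis of the endpoint. The reported 12-month rates are pulled in opposite directions and describe neither arm, and the time each lost patient was known to be alive is discarded.

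It also makes the two survival analyses disagree by construction. A patient lost at month 8 is censored at month 8 for overall survival, but is a death (Vx-001) or a survivor (placebo) at month 12. A 12-month result weaker than the survival curves could come from the rule alone.

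This was the trial's original primary endpoint (SAP 6), so its rates will be read beside the overall survival result.

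**Working it through.** **Inputs from the SAP.** 12-month survival of 43% on placebo and 58% on Vx-001; 100 evaluable and 110 randomised per arm; accrual of 39 months at 5.6 patients per month (sample-size section). One-sided 0.05 (5.1.2). Minimum follow-up of 6 months at the first lock (5.3.3). The share with missing 12-month status is not stated; I take 0 to 20% per arm as an assumed range.

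**Reproducing the plan's figure.** For the 12-month comparison the initial calculation claims "overall power of approximately 80% to detect a difference in treatment effect at the 0.1 one-sided significance level". With 43% vs 58%, 100 per arm and one-sided 0.10, the normal-approximation power for two proportions is 80.2%. The figure is reproduced. At the current one-sided 0.05, with nothing missing, it is 68.5% with 100 per arm and 72.1% with 110.

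**Effect of the rule.** Let m be the share in each arm whose 12-month status is actually missing, unrelated to outcome.

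- Vx-001: 0.58(1 − m)
- Placebo: 0.43(1 − m) + m = 0.43 + 0.57m
- Difference: 0.15 − 1.15m, which is zero at m = 0.15/1.15 = 13.0%

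Power = Φ[(d − 1.645·SE0)/SE1], where d is the imputed difference, SE0 uses the pooled rate and SE1 the separate rates. For m = 5% and 110 per arm: rates 0.551 and 0.4585, d = 0.0925, SE0 = 0.0674, SE1 = 0.0671, so power = Φ(−0.274) = 39%.

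| Actually missing per arm | Vx-001 | Placebo | Difference (points) | Power, 110 per arm |
|---|---|---|---|---|
| 0% | 58.0% | 43.0% | 15.0 | 72% |
| 2% | 56.8% | 44.1% | 12.7 | 60% |
| 5% | 55.1% | 45.9% | 9.3 | 39% |
| 10% | 52.2% | 48.7% | 3.5 | 13% |
| 13% | 50.5% | 50.4% | 0.05 | 5% |
| 20% | 46.4% | 54.4% | −8.0 | 0.2% |

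Under no effect (43% in both arms) with 5% missing, the rule creates a 5-point deficit for Vx-001. Rejection falls from 5% to 0.9% (100 per arm), so the test becomes conservative.

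**Assigned dropout is a different quantity.** In simulation (exponential survival, dropout uniform over 12 months), assigning 5% or 10% of patients to drop out leaves only about 3.6% or 7.2% actually missing, because some die first. With 110 per arm, power under the rule is then about 48% or 25%. A Kaplan-Meier comparison at 12 months (Greenwood variance, z-test) on the same kind of data keeps about 70%. With 100 per arm its mean difference stays at about 15 points. With nothing missing, the two methods have about the same power (about 71% with 110 per arm).

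**Timing, conditional.** Suppose the test were run at the first lock and patients not yet at week 52 were treated as missing.

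- Share entered in the last 6 of 39 months: 6/39 = 15.4%, or about 34 of 220.
- Mean survival over months 6 to 12: 0.535 on placebo and 0.667 on Vx-001.
- Alive with unknown status: 0.154 × 0.535 = 8.2% (9.1 patients) and 0.154 × 0.667 = 10.3% (11.3 patients), about 20 in all.
- Vx-001: 0.846 × 0.58 = 49.1%. Placebo: 0.846 × 0.43 + 0.082 = 44.6%. Difference about 4.5 points (4.4 in simulation).
- Simulated power is about 15%, against about 71% for Kaplan-Meier, with no loss to follow-up at all.

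**The case against.** The strongest reply is that little vital status will be missing. SAP 5.2.4.1 calls missing survival information rare, 5.2.4.1 and 5.2.4.3 require every effort to obtain it, and survival contacts every 12 weeks may be by phone. At 2% missing, 12.7 of the 15 points remain. This stands: full erasure needs 13% per arm, well beyond anything the SAP describes. The 10% in the sample-size section is the share excluded from the per-protocol set and must not be read as a missing-status rate.

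A reader might infer that everyone alive but short of week 52 at the first lock falls under the rule. The SAP does not say so. Section 5.2.4.3 concerns patients who miss the visit or are lost, and a visit not yet due is neither. The sample-size section continues follow-up to 12 months after the primary analysis, and 5.3.3 plans a second lock. What remains is that the lock for Table 22 is not named and that administrative censoring is not separated from loss.

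Section 5.3.5 lets only the primary analysis support definitive conclusions, and the rule works against Vx-001, so it cannot produce a false claim of efficacy. Both points stand and limit the severity. The primary Kaplan-Meier curves (Figure 2) will also show month 12 with proper censoring, although no 12-month comparison is drawn from them.

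Finally, SAP 6 deliberately keeps the chi-squared comparison. That is a reason to retain it, but not as the only 12-month analysis.

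**Conclusion.** The concern holds as a should-fix. The sole 12-month comparison is a bounding scenario presented as the analysis, and it treats patients of unknown status differently from the overall survival analysis. The planned difference shrinks by 1.15 points for each percentage point actually missing per arm. At 5% missing, power is roughly halved.

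These sizes assume the SAP's 43% and 58%, equal missing shares in both arms unrelated to outcome, and the one-sided 0.05 level of 5.1.2. (Section 5.3.5 would make this test two-sided, which needs reconciling.) They are a sensitivity range, not a forecast. The first-lock figures of about 20 imputed patients, about 4.4 points and about 15% power apply only if the test is run at that lock and patients not yet at week 52 are imputed; the documents establish neither. Nor do they support reading this as a threat to the trial's main conclusion, because the log-rank result is untouched.

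**What to change.** In SAP 5.2.4.3 and 5.3.2, make the difference in Kaplan-Meier survival at 12 months the main analysis of this endpoint, with Greenwood variance, a z-test and the SAP's own censoring rule for overall survival. Keep the chi-squared test with worst-case imputation as a labelled sensitivity analysis, limited to patients truly lost before 12 months and run once every patient has 12 months of potential follow-up. State that administratively censored patients are never imputed, and name the lock at which Table 22 is produced. Section 6 needs a matching line.

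The cost is wording in these sections and in Table 22, settled before unblinding; no new data are needed. The downside is reliance on non-informative censoring, which the primary analysis already assumes and which the retained sensitivity analysis would probe.
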